## Abstract

The emergence of the new coronavirus (COVID-19) at the beginning of 2020, considered a public health emergency due to its high transmission rate and lack of specific treatment, led many countries to adhere to social isolation. Although necessary, social isolation causes important psychological changes, negatively affecting the health of the population, including the older population. The aim of this study is to propose a 4-week, home-based physical exercise protocol for older people in social isolation and evaluate whether will promote positive changes in psychological variables such as anxiety, mood, depression, and stress, and in the variables sleep, quality of life, and physical capacities in the older adults. The sample will be selected in a probabilistic way from individuals aged 60 years or more from the city of Itajaí (Santa Catarina, Brazil). Of these, half will perform a home-based resistance training protocol, with 3 weekly sessions, for 4 consecutive weeks. For group allocation, patients will be randomized with a computer-generated 1:1 allocation to the physical exercise (PE) group or control group. Outcomes will be depressive symptoms, sleep quality, quality of life, stress, mood states, anxiety, and functional capacity, evaluated at baseline, after 4 weeks, and after 15 days of follow-up. This study will offer a home-based exercise protocol for older adults, with load progression and remote monitoring, thus filling a gap in the provision of PE in this population. The results will be able to identify possible improvements not only in physical health, but also in quality of life and mental health.

**Clinical Trial Registration:** The trial registration was carried out in the Brazil Clinical Trials Registry (RBR-5qh6f3v). (https://ensaiosclinicos.gov.br/rg/RBR-5qh6f3v).

## Introduction

The emergence of the new coronavirus (COVID-19) caused a pandemic considered a public health emergency by the World Health Organization (WHO). Due to the high transmission and lack of specific treatment, many countries have adopted restrictive measures, recommending social isolation and quarantine periods to contain the spread of the virus (Kraemer et al., 2020; World Health Organization [WHO], 2020a). Even today, there are countries that continue to recommend social isolation and prohibit agglomerations to avoid overloading health systems (Armitage and Nellums, 2020; Ferguson et al., 2020; Camuñas, 2021; Diotaiuti et al., 2021), this new situation implies challenges for different populations, such as athletes, workers and even the elderly (Andreato et al., 2020; Hernández-Hernández and Sancho-Gil, 2021).

Although necessary, social isolation causes important psychological changes, negatively affecting the health of the population, including the older population (Kenyon, 2020; Kraemer et al., 2020). With advancing age, a reduction in social interactions is common due to retirement and health conditions (Gao et al., 2018; Segel-Karpas et al., 2018), and this has been further aggravated during the COVID-19 pandemic. Studies indicate that being socially connected is related to positive outcomes of physical and psychological health and longevity in older adults (Gao et al., 2018; Segel-Karpas et al., 2018). More specifically, isolation is a risk factor for depression, anxiety disorders, stress, feelings of confusion, weakness, loneliness, anger, suicide, and worsening of existing psychiatric symptoms (Brooks et al., 2020; Sepúlveda-Loyola et al., 2020; Vindegaard and Benros, 2020; World Health Organization [WHO], 2020b).

In addition, social isolation facilitates a predominantly sedentary lifestyle, which is also associated with negative health effects (Reed et al., 2011; De Rezende et al., 2014; World Health Organization [WHO], 2020b; Reyna et al., 2021), implying a physical deconditioning, not only related to musculoskeletal levels, but the resulting negative metabolic changes (Montero et al., 2017; Bowden Davies et al., 2019), being related to greater chances of mortality, metabolic diseases, and cancer, among others (De Rezende et al., 2014; Gilchrist et al., 2020; Park et al., 2020). Therefore, strategies to reduce sedentary behavior in older adults are essential to improve quality of life, physical and mental health (Sepúlveda-Loyola et al., 2020; da Cruz et al., 2021) and physical deconditioning (Santy-Tomlinson, 2021).

Physical exercise (PE) is indicated to combat sedentary lifestyle, as well as being used as a means of prevention and treatment of several common diseases in aging, such as heart disease, diabetes, osteoporosis, hypertension, cancer, fibromyalgia, anxiety disorders, and depression (Debussche et al., 2012; Reif et al., 2013; Andrade et al., 2017a,b; Sties et al., 2018; da Silva et al., 2020). In addition, PE helps to promote health, providing an increase in quality of life (Haraldstad et al., 2017) and physical and psychological well-being (Andrade et al., 2018; Vilarino et al., 2021), and positively influencing affective and social relationships at all ages (Camuñas, 2021; Ni et al., 2016; Callow et al., 2020).

The need to keep the population physically active during isolation and social distancing has led to organizations such as the American College of Sports Medicine [ACSM] (2020), American Heart Association [AHA] (2020), American Physical Therapy Association [APTA] (2020), International Association of Physical Therapists working with Older People [IPTOP] (2021), and World Health Organization/EUROPE [WHO/EUROPE] (2020) to recommend the practice of PE remotely, such as online videos, applications, and online platforms for mobile phones and tablets through systems connected to the internet (Sepúlveda-Loyola et al., 2020). However, as far as we know, only one study was published verifying the effect of remote PE practice in older adults (Vitale et al., 2020). The authors showed positive results, indicating the possibility of performing PE remotely in this population, however, the topic needs further investigation.

Among the possibilities of PE practice during the period of social isolation, resistance training (RT) stands out, as it does not require equipment and can be performed without leaving the house and in small spaces. RT has numerous benefits for the older population, such as increased muscle strength, quality of life, and psychological well-being (Andrade et al., 2020; Vitale et al., 2020; da Cruz et al., 2021; Di Lorito et al., 2021). However, prescription and monitoring of RT remotely require different strategies, which should allow the same benefits as when monitored in person.

Thus, there is a need for studies that specify in detail the intervention used to provide guidelines for the practice of professionals. Furthermore, these studies should be controlled and randomized to reduce the risk of bias and increase safety regarding the expected effects on physical and psychological variables for the older population (Kenyon, 2020; Kraemer et al., 2020; Yamada et al., 2021). It was identified that there is no established protocol that indicates the best intensity, volume, and load progression and that presents parameters for monitoring and evaluation. Therefore, the creation and use of PE protocols for older adults through online technologies and with guidance from trained health professionals could represent an alternative to improve the physical and mental health of older adults during a period of isolation and social distancing, reducing psychological and affective disorders, which have been associated with increased morbidity caused by COVID-19 (Armitage and Nellums, 2020; Santini et al., 2020).

The hypothesis is that the remote PE protocol will promote changes in the psychological outcomes of depression, anxiety, mood states, and stress, and on the outcomes of sleep quality, quality of life, and physical abilities of older people in social isolation. In this sense, the aim of this study is to propose a 4-week (3x/week) home-based physical exercise protocol applied remotely to older people in social isolation.

## Materials and Methods

### Study Design

This is a protocol study for a randomized controlled trial (RCT), parallel-group, developed according to Standard Protocol Items: Recommendations for Intervention Trials (SPIRIT) (Chan et al., 2013) (Figure 1). This protocol was developed for a 4-week PE intervention and monitoring of a control group.

**FIGURE 1 F1:**
[figure not shown]
Flowchart demonstrating the participant selection process and the steps of the study protocol.

### Participants

The sample will be selected probabilistically with individuals aged 60 years and over from the city of Itajaí (Santa Catarina, Brazil). They will be recruited from a telephone directory of people registered with the Municipal Secretariat for the Promotion of Citizenship. Participants who meet the inclusion criteria will be randomized equally between two groups; the experimental group who will carry out the PE protocol (PEP) and the control group (CG) who will be instructed not to perform any type of PE and to follow their usual daily routines. For group allocation, patients will be randomized with a 1:1 computer-generated allocation^1^ and the researcher responsible for the randomization will not be involved in the evaluations.

To participate in the study, the following inclusion criteria will be respected: individuals of both sexes, aged ≥ 60 years (no maximum age limit); with internet access; able to understand and use the smartphone; with the physical and cognitive ability to understand and perform the exercises safely. The exclusion criteria will consist of elderly people who performed physical activity and/or exercise in the last 3 months, according to the criteria recommended by the World Health Organization (World Health Organization [WHO], 2011) (walks of 150 min per week and/or resistance training with weight for 75–150 min) and elderly people with any condition physical or cognitive that makes it impossible to practice the proposed exercises at home.

### Outcome Measures

The evaluations will be carried out before the beginning of the intervention, after 4 weeks of the intervention, and 15 days after the end of the intervention. In the initial assessment, a characterization questionnaire will be applied to obtain socioeconomic and health information.

The primary outcome will be the variable depression (Gorenstein and Andrade, 1996) and the secondary outcomes will be mood (Rohlfs et al., 2008), stress (Luft et al., 2007), sleep quality (Buysse et al., 1989; Bertolazi et al., 2009), quality of life (Power et al., 2005), anxiety (Beck et al., 1988) and physical abilities (Hlatky et al., 1989) of the older adults. The analyzed variables and the respective instruments are listed below in Table 1.

**TABLE 1 T1:** List of variables, instruments used, interpretation and reference.

Variables	Instruments	Interpretation of instruments/cutoff points	Authors (year)/articles
Depressive symptoms	BDI	These ups and downs are considered normal (1–10)/Mild mood disturbance (11–16)/Borderline clinical depression (17–20)/Moderate depression (21–30)/Severe depression (31–40)/Extreme depression (Over 40)	Gorenstein and Andrade (1996)/Validation of a Portuguese version of the BDI and State-Trait anxiety inventory in Brazilian subjects
Sleep quality	PSQI	Good sleep (0–4)/Sleep Disorder (5 or more)	Buysse et al. (1989)/The PSQI: a new instrument for psychiatric practice and research.
	Ese-Br	Scores above 10 suggest the diagnosis of excessive daytime sleepiness	Bertolazi et al. (2009)/Portuguese-language version of the Epworth sleepiness scale: validation for use in Brazil
Quality of life	WHOQOL—OLD	Need to improve (1–2.9)/Regular (3–3.9)/Good (4–4.9)/Very good (5)	Power et al. (2005). Development of the WHOQOL-old module
Stress	PSS	Scores can range from 0 to 56/Not the cut-off point.	Luft et al. (2007). Brazilian version of the Perceived Stress Scale: Translation and validation for the elderly
Mood states	BRUMS	Score can vary from 0 to 16/Not the cut-off point.	Rohlfs et al. (2008). BRUMS: an instrument for early detection of overtraining syndrome.
Anxiety	BAI	Scores between (0–21) indicates very low anxiety/(22–35) indicates moderate anxiety/A grand sum that exceeds 36 is a potential cause for concern.	Beck et al. (1988). An inventory for measuring clinical anxiety: Psychometric properties.
Functional capacity	DASI	The final score varies between zero and 58.2 points/Not the cut-off point.	Hlatky et al. (1989). A brief self-administered questionnaire to determine functional capacity (the Duke Activity Status Index).

*BAI, Beck Anxiety Inventory; BDI, Beck Depression Inventory; BRUMS, Brunel Mood Scale; DASI, Duke Activity Status Index; Ese-Br, Epworth Sleepiness Scale; PSQI, Sleep quality index (Pittsburgh); PSS, Perceived Stress Scale; WHOQOL—OLD, World Health Organization Quality of Life Group.*

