This gap in the literature can be filled with a systematic and specific home-based PE protocol through an RCT, as a form of non-pharmacological treatment to improve the physical and mental health of older adults, considering that PE practices are already established and considered beneficial on a large scale in international scientific publications (Lautenschlager et al., 2004). However, it is necessary to understand these data in a current scenario, with a perspective on the physical and mental health of older adults, through a PEP with safe remote monitoring. For this, the PEP was developed to meet current demands, promoting benefits in depression, anxiety, mood, sleep quality, stress, quality of life, and functional capacity.

The creation of this PE protocol through remote monitoring by health professionals will be an important ally to help prescribe PE for older adults in the midst of the pandemic caused by COVID-19. However, it has some limitations, including the difficulty of using and accessing technologies by the elderly population, which limits this intervention to those who have access and know how to use cell phones with internet. As there is no interaction at the time of exercise practice, attendance depends on the participant reports, considered a bias in the study. Another limitation, as this is an active intervention, it is not possible to blind the participants, which can also generate bias.

This protocol will serve as an excellent strategy for new public policies in several countries. Older people are a growing demographic group worldwide, but the increase in life expectancy must be accompanied by an equally good quality of life from these gained years. Physical activity certainly behaves as a protective factor at all ages, so this protocol could be very important to reach many elderly people who for various reasons cannot go to the gym but would be willing to follow this type of training at home. It is a unique PE protocol, developed in a systematic way, that is simple to perform, and requires little equipment and financial resources, thus contributing to its implementation and cost-effectiveness, and making it accessible to everyone.

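### BDI depression is the primary outcome in a sample not selected for symptoms, and neither the stated allocation nor the stated model uses baseline BDI severity, which costs precision and limits generalisation

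*Protocol article*

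**What the plan says.** Under Outcome Measures, "The primary outcome will be the variable depression". Table 1 gives the instrument as the BDI and its lowest bands as "These ups and downs are considered normal (1–10)/Mild mood disturbance (11–16".

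The Participants section includes "individuals of both sexes, aged ≥ 60 years (no maximum age limit); with internet access; able to understand and use the smartphone", together with the physical and cognitive ability to exercise safely. It excludes "elderly people who performed physical activity and/or exercise in the last 3 months" and people with a condition that rules out the exercises. People are "recruited from a telephone directory of people registered with the Municipal Secretariat for the Promotion of Citizenship". No BDI score, symptom or diagnosis is required, and none is excluded.

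On allocation, "patients will be randomized with a 1:1 computer-generated allocation"; no stratification factor is named. The Statistical Analysis section gives a two-way repeated-measures ANOVA with Bonferroni comparisons. Baseline is one of the time points, but baseline severity is neither a covariate nor a factor. Sample Size Calculation gives 56 participants plus 12 for dropout, with no target BDI difference. The Discussion presents the programme "as a form of non-pharmacological treatment to improve the physical and mental health of older adults" and counts depression among the outcomes it is meant to benefit.

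**The concern.** A participant who starts at 10 or less has few BDI points to lose. If such participants predominate, the mean difference between arms is pulled towards zero. A null result would then have two possible explanations, no effect or little room for one, and the stated analysis does not separate them.

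The participants with most room to improve are also those whose scores tend to fall most without treatment. In arms of about 34 they may split unevenly by chance. A model that uses baseline only as a time point does not correct for that regression to the mean. The stakes are a noisier primary estimate than necessary, and a conclusion that could be read as applying to people with depression when the sample was not selected for it.

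**Working it through.** **Inputs from the article.** Normal band up to 10 (Table 1); 56 participants, that is 28 per arm; 68 recruited, that is 34 per arm; alpha 0.05; power 0.95.

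**Assumed, because the article gives none.** Baseline BDI mean and SD, the share scoring 11 or more, and a baseline-to-follow-up correlation of 0.6.

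**1. The plan's own figure.** The 56 cannot be reproduced without an effect size, SD or test family. Solving backwards with 28 per arm and power 0.95:
- two-sided t-test: d = 0.98, which is 0.98 × 4 = 3.9 points at SD 4 and 0.98 × 6 = 5.9 points at SD 6;
- repeated-measures interaction with correlation 0.5: f ≈ 0.22 for three measurements, or 0.245 for two.

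The article does not say which applies, so the 56 does not show what BDI change the trial was sized for.

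**2. Room to improve.** Simulation with gamma-distributed BDI, floor at 0, 28 per arm, t-test on change, intended reduction 6 points:

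| Baseline mean / SD | Share at 10 or less | Realised effect | Power |
|---|---|---|---|
| 5 / 4 | 90% | 3.8 | 0.98 |
| 8 / 6 | 73% | 4.8 | 0.90 |
| 12 / 8 | 51% | 5.3 | 0.75 |
| 20 / 8 | 9% | 6.1 | 0.87 |

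The effect shrinks by 1 − 3.84/6 = 36% in the lowest row and not at all in the highest. Power does not fall with it, because low-scoring samples also vary less here.

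A proportional effect gives the same direction without any floor. Take means of 5 and 16 below and above the cut and a 30% reduction (1.5 and 4.8 points). The whole-sample effect is:
- 10% symptomatic: 0.9 × 1.5 + 0.1 × 4.8 = 1.83 points;
- 30% symptomatic: 0.7 × 1.5 + 0.3 × 4.8 = 2.49 points;
- 50% symptomatic: 0.5 × 1.5 + 0.5 × 4.8 = 3.15 points.

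**3. Chance imbalance.** Suppose 20 of 68 are symptomatic and allocation is 34:34. The number in one arm is hypergeometric with mean 10 and variance 34 × (20/68) × (48/68) × (34/67) = 3.58, so SD 1.89. The between-arm difference has SD 2 × 1.89 = 3.8. The exact 2.5% and 97.5% points for one arm are 6 and 14. A split of 6:14 or worse has probability 6%; 7:13 or worse, 18%.

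For mean BDI with 28 per arm, the baseline difference has SE √(2/28) = 0.27 SD, so a 95% range of ±0.52 SD. At correlation 0.6, regression to the mean carries 1 − 0.6 = 0.4 of that into the change comparison. At SD 6 the edge of the range is 0.4 × 0.52 × 6 = 1.2 points. Its expectation over randomisations is zero.

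**4. What using baseline BDI recovers.** The SD of a change-score comparison is proportional to √(2(1 − ρ)); with baseline BDI as covariate it is proportional to √(1 − ρ²). The ratio is √((1 + ρ)/2) = √0.8 = 0.894, a reduction of 10.6% at ρ = 0.6.

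I simulated 28 per arm with the first three baselines above. Reduction in the SD of the effect estimate, compared with unstratified, unadjusted change:
- stratified allocation at 10/11 with the stratum in the model: about 5–7% with no treatment effect, and 10–12% with a 30% proportional reduction;
- baseline BDI itself in the model: about 11–12% and 19–20%.

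Nearly all of this comes from the model term; stratified allocation alone adds little to it.

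**5. Effect by stratum.** With 10 and 24 per arm in the two strata and a common SD, the interaction has SE √(2/10 + 2/24) = 0.53 SD, so a 95% half-width of 1.04 SD. It could not settle whether the effect differs.

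**The case against.** The strongest reply is that an unselected sample fits the question asked. The Introduction's hypothesis concerns older people in social isolation, and it cites isolation as a risk factor for depression, so some raised scores are to be expected. The Abstract and Table 1 already call the outcome depressive symptoms. This stands.

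A reader might infer that the trial cannot speak to depression, or that a null result would be uninterpretable. The article supports neither. People with raised scores are eligible, no baseline distribution is given, and in the simulation the floor shrank the effect without by itself removing power. Nor must a positive result lie within the normal band, since symptomatic participants contribute to it. Whether a participant can change Table 1 category is beside the point, because the planned test compares means.

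A reader might also take the lack of stratification for a bias. It is not: randomisation balances BDI in expectation, and the test's error rate already allows for chance imbalance. Stratification detail may sit in the full protocol, which is not shown, so silence in a condensed article is no fault.

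What remains is that the eligibility list, the primary outcome and the model are stated, and together they leave a score already collected out of the primary comparison.

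**Conclusion.** The concern holds as a modest design point. The primary BDI comparison admits participants with little room to improve, and the stated allocation and model make no use of baseline severity. If baseline means are as low as 5 to 8, an intended 6-point effect falls to about 3.8 to 4.8 points. Using baseline BDI would cut the SD of the estimate by roughly 5–12% with the stratum, or 11–20% with the score itself at correlation 0.6, depending on the treatment effect. All of these sizes rest on assumed baseline distributions. The consequence is avoidable noise and a limit on generalising to people with clinical depression.

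**What to change.** Keep entry open. Complete and score baseline BDI before allocation, stratify the 1:1 allocation at 10 or less versus 11 or more, and include that stratum, or preferably baseline BDI itself, in the primary analysis. If the full protocol already stratifies, only the model term is needed, and it brings most of the gain.

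Report the BDI effect by stratum as descriptive only. Word the conclusion as depressive symptoms in older adults not selected for depression, and bring the Discussion into line.

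Cost: two allocation lists instead of one, one model term and one descriptive table, from a score already collected. The downsides are that the stratum estimates will be imprecise and that procedures may need reordering. The Control Group section describes the consent and baseline link going to people already allocated, so the sequence of baseline and allocation must be aligned across sections.

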### Adverse Events

Any adverse effects observed or reported by patients will be recorded and considered in the study results. In addition, these patients will be referred to medical care for proper treatment.

